### Study Procedure

#### Populations

Data will be assessed in the cohort and the nested case-control population (Textbox 1).

The following are the matching criteria for the nested case-control population: (1) type of procedure, (2) age, (3) BMI, (4) duration of procedure (as a percentile for this procedure), (5) diabetes, and (6) sex.

#### Study Sites

Approximately 13 surgical centers in Europe will be included in this study. To ensure adequate representation of each type of surgery, only centers with more than 10,000 surgeries will be considered. The distinction between academic and non-academic centers was chosen to ensure broad coverage and prevent selection bias.

Sites interested in participating will be identified through prior publications on SSI, prior SSI study participation, and membership in appropriate European scientific societies, including surgical, microbiological, and infectious diseases societies. Sites will be contacted and selected using a feasibility questionnaire (Multimedia Appendix 1) and procedure.

#### Target Population and Eligibility

All adult patients with a SSI after any surgical procedure—minimal invasive biopsies and eye surgery excluded—in 2016 will be part of our target population. Data from 2015 to 2017 will be collected if not enough data are available in 2015. The inclusion and exclusion criteria are shown in Textbox 2.

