**Methods:**

A retrospective, multinational, multicenter cohort study (*Staphylococcus aureus* Surgical Site Infection Multinational Epidemiology in Europe [SALT] study) with a nested case-control part will be conducted. The study will include all surgical procedures at a participating center in order to prevent selection bias and strengthen the understanding of SSI risk by determining the incidence for all common surgical procedures. Data will be assessed in the cohort population, including 150,000 adult patients who underwent any surgical procedure in 2016, and the case-control population. We will match patients establishing *S. aureus* SSI 1:1 with controls from the same center. Data on demographics, surgery, and microbiology will be exported from electronic files. More detailed data will be captured from the case-control population. The SALT study will include 13 major or academic surgical centers in Europe, comprising 3 in France, 4 in Germany, 2 in Italy, 3 in Spain, and 1 in the United Kingdom. Sites were selected using a feasibility questionnaire.

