#### Retrospective Record

Data from all patients undergoing any surgical procedure—minimal invasive biopsies and eye surgery excluded—will be collected retrospectively. Collection will be performed by surveying electronic health records (EHRs) and databases from all participating sites (Figure 1).

Administrative and microbiological data will be accumulated to identify the target population.

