##### Detection of
*S. aureus* Surgical Site Infection

As a first step, we will export the data listed in the Data Collection Cohort section from all patients who underwent surgery in each center in 2016. We expect a minimum of 100,000 cases to be included in the cohort. *S. aureus* SSI that occurred in 2016 will be detected using microbiological data. 

To ensure feasibility, only centers with the capability of electronic microbiologic data export will participate. All patients presenting a *S. aureus* infection from the following will be identified: (1) wound swabs, (2) aspirates, (3) samples obtained during surgery, and (4) blood cultures.

Subsequently, electronic matching with clinical data will be performed in order to determine those patients who underwent a surgical procedure and had an *S. aureus* infection. This approach provides a sensitivity of 100% for identification of proven *S. aureus* SSI cases.

Data collected for surgical site infection cases.Length of hospitalizationLength of intensive care unit (ICU) stayReason for ICU stay; attribution to surgical site infections (SSI)Hours of mechanical ventilationHemodialysisSurvival at 30 and 90 daysIn case of death, attribution to SSINecessity for revision surgeryIn case of SSI, attribution to SSINecessity for readmissionIn case of readmission:ReasonAttribution to SSILength of hospitalizationLength of ICU stayHours of mechanical ventilationAll antibiotic treatments, including duration and dosageAll antibiotic treatments, including durationFunctional status at admission and at final dischargeCausative pathogens including resistance patternsType of SSI according to European Centre for Disease Prevention and Control criteria

All patients identified will be documented manually. Occurrences of SSI will be verified on a case-by-case following the criteria of the Hospital Acquired (HAI) SSI protocol [1].

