#### Primary Analysis

The primary objective of this study is to determine the overall and procedure-specific incidence of *S. aureus* SSI in Europe. The primary analysis will consist of calculating the incidence using 95% CIs.

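### The eligibility section contradicts the all-surgery 2016 cohort and ties the 2015–2017 fallback to the wrong year, and SSI detection by calendar year conflicts with the follow-up window

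*Protocol article*

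**What the plan says.** Target Population and Eligibility gives the target population as "All adult patients with a SSI after any surgical procedure" in 2016, with biopsies and eye surgery excluded. Its next sentence is the fallback: "Data from 2015 to 2017 will be collected if not enough data are available in 2015".

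Other sections of the protocol article describe a different population:

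- Abstract, Methods: a cohort "including 150,000 adult patients who underwent any surgical procedure in 2016".
- Retrospective Record: "Data from all patients undergoing any surgical procedure", with the same two exclusions.
- Detection of S. aureus Surgical Site Infection: the export is taken "from all patients who underwent surgery in each center in 2016".
- Textbox 2: the only inclusion criterion is adult age at surgery. An SSI is mentioned only as an exclusion, when already present at surgery.

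On timing, the detection section says that S. aureus "SSI that occurred in 2016 will be detected using microbiological data". The Cohort part of Data Collection instead records SSIs related to the observed procedure within 90 days. The Deep Incisional and Organ Space definitions run to 30 days, or to one year if an implant is in place.

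Under Primary Analysis, "The primary analysis will consist of calculating the incidence using 95% CIs".

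**The concern.** An incidence needs everyone at risk in the denominator, and a numerator that follows each of those people for the same length of time. The eligibility section unsettles the first requirement and the detection section the second.

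A target population of patients with an SSI is selected on the outcome, so no incidence can be calculated from it.

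The fallback decides which calendar years a center contributes. Read literally, a center with ample 2016 data and thin 2015 data would widen its window, while a center short of 2016 data but complete for 2015 would not. That is the reverse of what a fallback for a 2016 cohort is for.

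Counting SSIs by the calendar year of infection gives patients operated on late in 2016 a shorter observation period than those operated on early in the year. Their infections in early 2017 would not be found, and the primary incidence would be too low.

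**Working it through.** **1. Which denominator the plan's own figures use.** Sample Size gives a 1.5% rate, 150,000 patients and 2250 cases: 0.015 × 150,000 = 2250, as stated. It also gives 1500 procedures for ±0.5% at a 1% rate. The half-width is 1.96 × √(0.01 × 0.99 / 1500) = 0.504%, and exactly 0.5% would need 1522 procedures, so 1500 is a fair rounding. Both calculations count operated patients, not infected ones. They agree with the Abstract, Retrospective Record, Textbox 2 and the detection section, and they disagree with the eligibility sentence.

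**2. Which year is the base year.** It is 2016 in the Abstract, in the first sentence of the eligibility section itself, and in the detection section. The year 2015 appears only in the fallback sentence, which is also the only place where the fallback is mentioned. Nothing elsewhere lets a reader correct the trigger.

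**3. Loss from counting only SSIs that occurred in 2016.** Inputs from the article: surgery in 2016 (366 days) and windows of 30 and 90 days. Assumptions: surgery dates are uniform over the year, and delay to infection is uniform over a window of W days. An SSI is missed if surgery day plus delay runs past day 366, so

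share missed = mean delay / 366 = W / (2 × 366).

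- W = 30: 30 / 732 = 4.1%
- W = 90: 90 / 732 = 12.3%

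Infections in early 2016 after surgery in late 2015 do not offset this, because the export holds only patients operated on in 2016 and the microbiology is matched to that export.

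**4. Size on the plan's scale.** Take 1.5% and 2250 cases as the true values after 2016 surgery.

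- W = 30: 2250 × 0.041 ≈ 92 cases missed; the observed rate is 1.5% × (1 − 0.041) = 1.44%.
- W = 90: 2250 × 0.123 ≈ 277 cases missed; the observed rate is 1.5% × (1 − 0.123) = 1.32%.

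The shortfall is 0.06 to 0.18 percentage points. The simple binomial half-width of the overall rate is 1.96 × √(0.015 × 0.985 / 150,000) = 0.06 percentage points. The bias is therefore about one to three times the planned sampling error of the overall estimate, ignoring any variation between centers.

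The one-year implant window would lose more. I give no figure, because uniform delay over a full year is a poor assumption and the article offers nothing better.

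**The case against.** The strongest defence is that the eligibility section does not control the data. The export rule is in the detection section and covers all 2016 surgery, and Textbox 2, to which the eligibility section itself refers, requires no SSI. The term may also mean the infected patients found within the cohort, since Retrospective Record says "Administrative and microbiological data will be accumulated to identify the target population". Most of this stands. A reader might infer that the incidence will be calculated among infected patients only, or that sites will export only those patients, and the documents do not support either. The defence does not clear the wording, though: the sentence says any SSI where the cases are S. aureus SSIs, and it introduces criteria that apply to operated patients.

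A reader might also infer that a center using the fallback would report about a third of its true rate, with three years of procedures set against one year of infections. That requires widening the denominator while holding detection at 2016. The detection section describes the base case, where both are 2016, and no text says that only one of them would be widened. The threefold bias is a risk to close off, not a stated plan.

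On detection, the 90-day item in the Cohort section suggests that SSIs were meant to be tied to the procedure. However, that list is said to be for description only, while cases are found through the microbiology search, and only patients identified there go on to manual verification. An infection outside the search period would not reach that step.

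The 4% to 12% range also has a fair challenge. The Limitations in the Discussion concede that in-patient laboratory data miss post-discharge infections, so detectable delays may be short. The loss is proportional to mean delay, and early-clustered infections would bring it to the lower end or below.

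Finally, what counts as not enough data may be left to the full protocol. Its absence from an article is no part of this point.

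**Conclusion.** The point holds as a contradiction in the text plus one rule that affects the count.

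- **Population wording:** contradicted by the other sections, which show the intended denominator. No sample-size figure changes.
- **Fallback trigger:** wrong as written and corrected nowhere. 2016 is presumably meant. It matters only at a center that needs the fallback, and the article does not say that any center does.
- **Detection by calendar year:** conflicts with the 90-day follow-up, and with the one-year implant window. It loses about 4% to 12% of SSIs after 2016 surgery if followed literally, given uniform surgery dates and uniform delay over 30 or 90 days. The loss is larger if a center uses the fallback and detection is not widened with it.

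This should be corrected, because incidence is the primary objective and the correction is cheap. It is not evidence that the analysis will use the wrong denominator.

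**What to change.** 1. In Target Population and Eligibility, define the target population as all adults undergoing any eligible surgical procedure in 2016, and name S. aureus SSI as the outcome.
2. Make the 2015–2017 fallback depend on insufficient data for 2016.
3. In the detection section, count an SSI by the date of its index procedure plus the follow-up window that applies to it, not by the calendar year of infection. Extend the microbiology export past the end of the procedure period: for surgery up to 31 December 2016, to 31 March 2017 for 90 days, or to the end of 2017 where the one-year implant window applies. A center that uses the fallback extends the export over the added years in the same way.

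The cost is a few corrected sentences and a slightly wider microbiology export. The sample-size calculation stays as it is.

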**Figure 1 figure1:**
[figure not shown]
Data assessment and matching procedure. ASA: American Society of Anesthesiologists; BMI: body mass index.

Data assessed in the cohort and nested case-control population.Cohort populationExport of electronic file data on demographicsSurgical procedure codeDuration of procedureAmerican Society of Anesthesiologists scoreBody mass indexComorbidity International Statistical Classification of Diseases and Related Health Problems codesWound class of all patients undergoing surgeryNested case-control: for patients establishing *S. aureus* surgical site infections (SSI) and 1:1 matched controls from the same centerLength of hospitalizationLength of intensive care unit (ICU) stayReason and attribution to SSISurvival at 30 and at 90 daysAntibiotic treatments including duration, functional status at admission and at final discharge, necessity for surgical revision, and death attributed to SSIIf readmission is necessary, the following will be recorded:Reason and attribution to SSILength of hospitalizationLength of ICU stayAntibiotic treatments and their duration

Inclusion and exclusion criteria.InclusionAge 18 years or greater at the time of surgeryExclusionPatients undergoing minimal invasive biopsies and eye surgerySSI at the time of surgeryCases with missing data defined as missing completely at random

#### Time Schedule

The time schedule for the study is shown in Figure 2.

#### Sample Size

We assume a 1.5% incidence rate of *S. aureus* SSI. Incidence rates can be determined with a 95% CI of plus or minus 0.5% by observing 1500 surgical procedures, assuming a mean *S. aureus* SSI rate of 1%. Lower incidence rates would result in smaller 95% CIs with a similar sample size or similar CIs with a smaller sample size. Therefore, at least 15 centers should be included in the analysis, resulting in 90,000 to 150,000 patients observed patients. This will allow us to calculate incidence rates with meaningful precision for all surgical procedures performed on at least 1% to 1.5% of respective patients. To further broaden the scope of this study, 1 or 2 centers per country will be included specializing in types of surgery not traditionally performed at academic surgical centers but highly relevant to the prevention of SSI in otherwise healthy patients (eg, plastic surgery). Assuming a 1.5% incidence rate of *S. aureus* SSI, in a population of 150,000, 2250 cases will be matched to 2250 controls.

#### Data Collection

##### Cohort

The following variables will be collected from EHRs for descriptive purpose only: (1) age by category; (2) sex; (3) BMI; (4) comorbidities (International Statistical Classification of Diseases and Related Health Problems [ICD-10] codes); (5) diabetes; (6) type of procedure; (7) duration of procedure; (8) occurrence of SSI related to observed procedure within 90 days, including date of diagnosis; (9) wound class.

**Figure 2 figure2:**
[figure not shown]
Study timelines. SAP: Statistical Analysis Plan; IRB: institutional review board; ECCMID:European Congress of Clinical Microbiology and Infectious Diseases; SSI: surgical site infections.

##### Surgical Site Infection Cases

SSI cases will be identified through EHR review in conjunction with microbiological data. The data recorded is shown in Textbox 3.

##### Detection of
*S. aureus* Surgical Site Infection

As a first step, we will export the data listed in the Data Collection Cohort section from all patients who underwent surgery in each center in 2016. We expect a minimum of 100,000 cases to be included in the cohort. *S. aureus* SSI that occurred in 2016 will be detected using microbiological data. 

To ensure feasibility, only centers with the capability of electronic microbiologic data export will participate. All patients presenting a *S. aureus* infection from the following will be identified: (1) wound swabs, (2) aspirates, (3) samples obtained during surgery, and (4) blood cultures.

Subsequently, electronic matching with clinical data will be performed in order to determine those patients who underwent a surgical procedure and had an *S. aureus* infection. This approach provides a sensitivity of 100% for identification of proven *S. aureus* SSI cases.

Data collected for surgical site infection cases.Length of hospitalizationLength of intensive care unit (ICU) stayReason for ICU stay; attribution to surgical site infections (SSI)Hours of mechanical ventilationHemodialysisSurvival at 30 and 90 daysIn case of death, attribution to SSINecessity for revision surgeryIn case of SSI, attribution to SSINecessity for readmissionIn case of readmission:ReasonAttribution to SSILength of hospitalizationLength of ICU stayHours of mechanical ventilationAll antibiotic treatments, including duration and dosageAll antibiotic treatments, including durationFunctional status at admission and at final dischargeCausative pathogens including resistance patternsType of SSI according to European Centre for Disease Prevention and Control criteria

All patients identified will be documented manually. Occurrences of SSI will be verified on a case-by-case following the criteria of the Hospital Acquired (HAI) SSI protocol [1].

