###### Superficial Incisional

Infection occurs within 30 days after the operation and involves only skin and subcutaneous tissue of the incision and at least 1 of the following: (1) purulent drainage with or without laboratory confirmation, from the superficial incision; (2) organisms isolated from an aseptically obtained culture of fluid or tissue from the superficial incision; (3) at least 1 sign or symptom of infection (pain or tenderness, localized swelling, redness, or heat and superficial incision is deliberately opened by surgeon, unless incision is culture-negative); and (4) diagnosis of superficial incisional SSI made by a surgeon or attending physician.

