###### Deep Incisional

Infection occurs within 30 days after the operation if no implant is left in place or within 1 year if the implant is in place and the infection appears to be related to the operation and infection involves deep soft tissue (eg, fascia, muscle) of the incision and at least 1 of the following: (1) purulent drainage from the deep incision but not from the organ/space component of the surgical site; (2) a deep incision spontaneously dehisces or is deliberately opened by a surgeon when the patient has at least 1 sign or symptom (fever greater than 38° C, localized pain or tenderness, unless incision is culture-negative); (3) an abscess or other evidence of infection involving the deep incision is found on direct examination, during reoperation, or by histopathologic or radiologic examination; or (4) diagnosis of deep incisional SSI made by a surgeon or attending physician.

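### Denominator set by surgery in 2016, numerator by infection in 2016: followed as written, the primary incidence is biased low, most for implant surgery

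*Protocol article*

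**What the plan says.** All references are to the protocol article.

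- **Denominator.** The abstract (Methods) describes the cohort as "150,000 adult patients who underwent any surgical procedure in 2016". The section on detection of S. aureus SSI exports data "from all patients who underwent surgery in each center in 2016".
- **Numerator.** The same paragraph of that section says that S. aureus "SSI that occurred in 2016 will be detected using microbiological data". Positive cultures are then linked electronically to the surgical data, and the approach is credited with 100% sensitivity for proven cases.
- **Case definition.** Identified patients are verified individually. Superficial: "Infection occurs within 30 days after the operation and involves only skin and subcutaneous tissue". Deep incisional and organ/space: 30 days without an implant, otherwise "within 1 year if the implant is in place and the infection appears to be related to the operation".
- **Cohort data field.** Data Collection, Cohort lists "occurrence of SSI related to observed procedure within 90 days, including date of diagnosis" among variables that "will be collected from EHRs for descriptive purpose only".
- **Fallback.** Target Population and Eligibility sets 2016 as the year of surgery and adds: "Data from 2015 to 2017 will be collected if not enough data are available in 2015".
- **Primary analysis.** Overall and procedure-specific incidence with 95% CIs.

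**The concern.** An incidence proportion needs every member of the denominator to be followed for the whole risk window. Here the risk window starts at surgery, but the stated search ends with the calendar year. A patient operated on in December 2016 and infected in January 2017 meets the case definition and is still not a case. Infections in early 2016 after surgery in 2015 do not put this right: those patients are outside the exported cohort, and if they were counted anyway they would be cases without a denominator.

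The loss grows with the time from surgery to infection, so it differs between procedures. That matters because the Introduction aims to show that the S. aureus SSI rate does not depend on the procedure. A cut-off that removes more cases from implant surgery than from other surgery distorts exactly that comparison. It is also incompatible with the claimed 100% sensitivity, since a culture-proven infection in January 2017 would never be searched for.

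**Working it through.** **The plan's own figures.** Sample Size and Statistical Analysis give a 95% CI of ±0.5 points from 1500 procedures at a 1% rate, and 2250 cases at 1.5% in 150,000.

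- n = 1.96² × 0.01 × 0.99 / 0.005² = 1521, close to 1500. The half-width at n = 1500 is 0.504 points.
- 0.015 × 150,000 = 2250.

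Both reproduce.

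**Loss from the calendar rule.** Assume surgery dates are uniform over the 366 days of 2016. Let T be the days from surgery to infection. An infection at T falls in 2017 with probability T/366, so the share of cases lost is E[T]/366. The document gives no distribution for T, so the following are assumptions. For an exponential with scale s truncated at window W, E[T] = s − W·e^(−W/s)/(1 − e^(−W/s)).

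| Window | Assumed onset | E[T], days | Lost (E[T]/366) | 1.5% becomes |
|---|---|---|---|---|
| 30 days | exponential, scale 15 | 10.3 | 2.8% | 1.46% |
| 30 days | uniform | 15.0 | 4.1% | 1.44% |
| 1 year (implant) | exponential, scale 30 | 30.0 | 8.2% | 1.38% |
| 1 year (implant) | exponential, scale 60 | 59.2 | 16.2% | 1.26% |
| 1 year (implant) | exponential, scale 90 | 83.6 | 22.8% | 1.16% |
| 1 year (implant) | exponential, scale 120 | 101.7 | 27.8% | 1.08% |
| 1 year (implant) | uniform | 182.5 | 49.9% | 0.75% |

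**Overall effect.** The share of SSIs under the 1-year window is not given either. If it is 10 to 30%, and the remainder lose 4.1%:

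- Low end: 0.9 × 4.1% + 0.1 × 8.2% = 4.5%, that is 1.5 × 0.045 = 0.07 points.
- High end (uniform implant onset): 0.7 × 4.1% + 0.3 × 49.9% = 17.8%, that is 0.27 points.

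**Against random error.**

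- Overall: the half-width at 1.5% and N = 150,000 is 1.96 × √(0.015 × 0.985 / 150,000) = 0.0615 points, or 4.1% relative. This is computed here and not stated in the article.
- Procedure level: the stated precision is ±0.5 points at 1%. A loss of 3 to 28% is 0.03 to 0.28 points at that rate, inside the interval.

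**The 90-day field.** If this field limited capture, the share of 1-year-window infections lost would be P(T > 90): 5.0%, 22.1%, 35.7% and 44.6% for scales 30, 60, 90 and 120, and 75.3% for uniform onset. Nothing is lost with a 30-day window.

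**The case against.** The strongest reply is that one loosely worded sentence carries the whole calendar cut-off. Other parts of the article tie follow-up to the operation: the 90-day SSI field, survival at 90 days and readmissions all need 2017 records for patients operated on late in 2016. The list of specimen types to be searched carries no date limit, and the linkage sentence names no year. The authors may have meant SSI in the 2016 cohort. This is fair, and it is why the bias is stated here as following from the text as written. It does not remove the conflict, because the only dated statement about detecting the numerator says 2016.

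Three stronger readings are tempting, and the document does not support them.

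- **That the 90-day field cuts implant cases out of the primary numerator.** The field is labelled descriptive, and cases are verified under the 30-day and 1-year criteria. It excludes infections after day 90 only if it limits capture, so its loss should not be added to the calendar loss as one established bias.
- **That the bias exceeds the study's stated random error.** The stated figure is ±0.5 points per 1500 procedures, and most of the assumed losses fall inside it. Even against the computed overall half-width of 4.1% relative, the 2.8% loss for a 30-day window is smaller.
- **That large losses are established.** They arise only under assumed onset times for implant infections.

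Two passages might be thought to cover the point. The Limitations in the Discussion concede that late post-discharge infections are missed because only in-patient laboratory data are used. That is a different mechanism, though it means a longer export will not recover every lost case. The 2015 to 2017 fallback is triggered by insufficient data and does not extend follow-up of 2016 surgery.

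**Conclusion.** The concern holds in this form. The stated numerator and denominator use different clocks. Followed as written, the primary incidence is biased low, and more so where the 1-year implant window applies. Those two statements need only that some infections after 2016 surgery begin in 2017, that cases are linked to the 2016 cohort as described, and that infections counted under the longer window tend to occur later.

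The size is not established. It rests on uniform surgery dates and assumed onset distributions: about 3 to 4% relative with a 30-day window, roughly 8 to 28% with the 1-year window, and 50% at the extreme of uniform onset. The bias does not shrink with sample size, so it weighs most on the overall estimate and on large procedure groups, where the CI is narrow.

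The mismatch between the 90-day field and the 1-year criterion is a separate inconsistency that needs resolving, with an effect on the primary result only if the field governs capture.

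**What to change.** 1. Define a case as an S. aureus SSI whose index surgery lies between 1 January and 31 December 2016 and whose onset lies inside the stated case-definition window, and delete the calendar-year condition on the infection.
2. Export microbiology from 1 January 2016 through 31 December 2017, so that surgery on the last day of 2016 is covered for a full year.
3. Reconcile the 90-day cohort field with the 30-day and 1-year criteria, and state which rule governs the primary numerator.
4. Correct the year in the fallback rule, whose trigger refers to 2015 although the target year is 2016.
5. Withdraw or qualify the 100% sensitivity claim.

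The cost is protocol wording, a longer date range in an electronic export, and manual documentation of the recovered cases. The timetable allows it: recruitment is to end in February 2018 and the database is to close in September 2018, both after the end of 2017. Late infections diagnosed outside the hospital will still be missed, as the article already states.
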